## Abstract

**Background:**

Hearing loss and tinnitus are prevalent in America, and noise-induced hearing loss is a leading cause of hearing loss. Noise-induced hearing loss has negative impact on quality of life, physical and emotional functioning, social life, and employment. In addition, noise-induced hearing loss results in heavy social and economic burdens on families and communities from all ethnic and socioeconomic groups. Farmers are a group that is particularly high risk for noise-induced hearing loss, and is underserved by programs designed to limit that risk. They are among the most noise-exposed group of workers, and experience the second highest prevalence of noise-induced hearing loss among all occupational categories. In agriculture, 1.5 million workers (43.3%) report exposure to hazardous noise. Although use of hearing protection devices (HPDs) would protect them from noise-induced hearing loss, use among farmers is low.

**Methods/Design:**

The purpose of this project is to compare the effectiveness of several approaches to influencing hearing protector use. Approaches include: a) an interactive, predictors-based intervention delivered via the Internet; b) a static informational web site; and c) a mailed sampler of hearing protectors. The goals are to further develop an intervention to promote farmers’ use of HPDs, and compare the effectiveness of the interventions delivered in various combinations. Participants will include 701 farmers. Sites will be affiliates of a major farmer organization. Data will be collected at baseline, 6, and 12 months. A random intercept mixed model will be used to explore the fixed effects of the three NIHL prevention interventions over time while adjusting for age and gender. This project will involve a partnership between the University of Michigan and a major farmer organization to accomplish project aims.

**Discussion:**

Results of this study will be used to inform future research-to-practice studies to increase hearing protector use. Increased use of hearing protectors is expected to reduce rates of noise-induced hearing loss and other negative effects of high noise exposure, and improve quality of life in this high-risk and underserved group.

**Trial registration:**

Clinicaltrials.gov NCT01454895 Registered 14 October, 2011.

## Background

Noise-induced hearing loss (NIHL) is highly prevalent among US workers, particularly among farmers. An estimated 22 million workers are exposed to hazardous noise at work [1] and NIHL is among the most common work-related diseases, and the second-most self-reported occupational disease or injury [2]. Estimates of prevalence rates for NIHL among farmers vary greatly, and have been reported to be 17% [3], 22% [4], 38% [5], 65% [6], and 72% [7]. In comparison studies, farmers were more likely to have hearing loss than non-farmers [3,6,8].

NIHL is characterized by loss of hearing in higher frequencies; it is permanent and incurable, and typically progresses slowly and insidiously with continued exposure to high levels of noise. Most people are unaware that they are affected until it is already moderately severe [9].

NIHL has negative impact on the quality of life of the affected individuals as well as their families and communities, affecting physical and emotional functioning, social life, and employment. In addition, persons with NIHL frequently experience tinnitus, and have increased safety risks due to difficulty hearing warning sounds [10]. Importantly, hearing loss has also been associated with increased risk for injury among farmers [11].

Treatments for NIHL are limited and unsatisfactory, indicating that primary prevention offers the best option for success. Because NIHL is permanent and irreversible, treatment is limited to hearing aids for sound amplification. Most users find hearing aids expensive, unlike their natural hearing, and particularly unsatisfactory when there is background noise or when trying to focus on one speaker when there are other competing sounds [12].

Systems to protect workers from NIHL are not present in the farm work setting. Farmers are unique in that unlike workers in general industry, most farmers are not protected by the OSHA Hearing Conservation Standard (i.e., noise level monitoring and a hearing conservation program for at-risk employees which includes audiometric testing, training, and provision of hearing protection devices) [13]. Also, because most farms in the US are small, family-run organizations, there is no labor advocacy for worker hearing health and work-based health programs [14]. Many farmers may underestimate their exposure to noise hazards and consequences of noise exposure, and may not be knowledgeable about NIHL prevention techniques.

Noise elimination is the most preferred method of prevention of NIHL. However, this approach is often not technically or economically feasible in the farm work environment [14]. Consistent use of hearing protection devices is effective in preventing NIHL [15-17]. While there are several types of hearing protectors marketed (e.g., foam plugs, ear muffs), there is no “best” type of hearing protection; the “best” is the one the user prefers and will wear.

The problem of NIHL has been identified as a priority by federal agencies, including Healthy People 2020 [18], the National Institute for Occupational Safety and Health [19], and the National Institutes for Deafness and Communication Disorders [20].

There is evidence that interventions are needed, and can be successful in relieving this problem without negative impacts and at low costs. Use of hearing protectors is an effective method of preventing NIHL when engineering or administrative controls are not feasible or economical [21-23]. Epidemiological studies show that the need for interventions to increase hearing protector use among farmers is high, and that unlike some other worker groups, there is no ceiling effect limiting effectiveness of interventions [24-26]. Studies have identified predictors of hearing protector use among farmers, and have demonstrated that farmers are interested in increasing their use of hearing protectors [25]. Predictors-based and Internet-based interventions have been effective in other groups [27-31], and the proposed study seeks to apply this existing research to a test of interventions for farmers, a high risk and underserved group.

The proposed study takes advantage of existing organizations of farmers by partnering with the single largest farm organization in the US. This partnership will serve to optimize recruitment and retention of participants while minimizing costs. Members of the farm organization are farm operators; many are employers of farm laborers and therefore influential in determining the use of hearing protectors by laborers.

The proposed study will answer important questions in development of behavioral interventions to widely dispersed populations. It will connect with participants through their trade association together with using Internet-based health information. These methods have potential for reaching an otherwise difficult-to-reach rural and widely dispersed population. Together with an efficacious intervention, the program has potential for excellent health impact. Results from the proposed study will provide a model for future behavioral intervention research in a dispersed population and create new approaches for the prevention of NIHL, a serious preventable impairment.

### Theoretical framework: the farmers’ use of hearing protection model

A variety of factors have been found to be predictors of HPD use in multiple studies of workers, including farmers. These factors are included in the Farmers’ Use of Hearing Protectors Model (Figure 1), and serve as a guide for the proposed study. In a previous study [25], this parsimonious model was effective in predicting HPD use in 74% of cases.

**Figure 1 Fig1:**
[figure not shown]
Predictors of farmers’ use of hearing protection model.

Perceived Barriers to HPD Use are impediments [32] resulting in discomfort or difficulty in communication, and have consistently shown a negative and significant relationship to HPD use in studies of factory workers [33], construction workers [32,34], and farmers ([24,25,35], [name].: Farmers’ preference for use of hearing protectors, unpublished), Perceived Benefits of HPD Use are users’ ideas about the positive consequences of HPD use. Benefits were found to be positively related to HPD use in studies of factory and construction workers [32,33] and farmers [24]. Availability (and accessibility) of HPDs have had a positive and significant relationship to HPD use in studies of industrial workers [33] and farmers [24,25,35]. Self-efficacy of HPD Use is the extent to which an individual has confidence in one’s own ability to use HPDs [32], has had a positive and significant relationship to HPD use in studies of factory [33] and construction workers [32]. Two studies of farmers [24,25] showed a positive, but non-significant relationship between self-efficacy and HPD use. Interpersonal Influences are the individual’s perceptions of the behaviors, beliefs or attitudes of others, operationalized in three subscales: Interpersonal Norms, Modeling, and Support [32]. Interpersonal Norms are the respondents’ beliefs about how much others think they should wear hearing protection. Interpersonal Support refers to encouragement or praise from family, friends, and coworkers about the respondents’ use of hearing protection. Interpersonal Modeling is how much respondents believe family members and other farmers use hearing protection when exposed to noise. Administration of the Farmers’ Interpersonal Influences on Use of HPDs Scales (“Norms,” “Modeling,” and “Support”) showed significant and positive relationships to HPD use in the convenience sample of farmers [24], but not in a random sample of farmers [25].

Demographic Factors (age and gender) are non-modifiable factors, but important to assess. In one survey of farmers [24], women reported use of HPDs more frequently, while other studies [25,36] indicated men are more frequent users. Age was found to have a non-significant relationship to HPD use in two studies [24,25]. There are no published studies examining the relationship between race or ethnicity and HPD use.

A limited number of studies have found other factors (e.g., noise annoyance [37], perceived susceptibility to NIHL [37], perception that health problems were preventable [35]) to have a significant relationship to HPD use in non-farming samples. Perceived negative effects of NIHL on family was significantly related to HPD use in a sample of farmers [26].

## Methods

### Overview of design and methods

The purpose of this project is to identify interventions that will increase the use of HPDs, thereby reducing NIHL. The specific aim of this study is to contrast the effects of three alternative strategies (“Interactive Web,” IWI a “Static Web,” SWI, and a sampler of HPDs, HPD I) in various combinations, on HPD use and use-related attitudes/beliefs. The study uses a randomized-controlled design. It will be conducted in partnership with a major farmer organization. The University Health and Behavior Science IRB reviewed the study protocol and determined that it is exempt from ongoing IRB review.

### Sample, enrollment, and retention

Participants in this study will be farm operators age 18 or older, who are active in production at least 20 hours per week on average, have ability to read English, and have computer and Internet access. A farm operator is the person who runs the farm, making the day-to-day decisions [38].

One or more study team members will attend selected farm trade group meetings to recruit subjects. Recruitment will continue until the enrollment quota is met. Prospective subjects will log onto a designated Web site, where the enrollment process will be managed. In addition to the data collected from direct user entry during enrollment, metadata will also be collected for use in later analysis.

### Random assignment to study conditions

After participants provide informed consent and enroll in the study, they will be assigned to the five study conditions (Table 1) by a random assignment of treatments in blocks produced by Stata software [39]. Recruitment will continue until the enrollment quota is met, resulting in five approximately equal-sized groups.

**Table 1 Tab1:** **Study Conditions**

**Group**	**Observation**	**Intervention**			**Observations**
		**Interactive web information**	**Static web information**	**HPDs**	
1	Pretest	X		X	Post-tests at 6 & 12 months
2	Pretest	X			Post-tests at 6 & 12 months
3	Pretest		X	X	Post-tests at 6 & 12 months
4	Pretest		X		Post-tests at 6 & 12 months
5	Pretest			X	Post-tests at 6 & 12 months

### Follow-up

At 6 and 12 months, participants in all five groups will receive an invitation by e-mail to log on to complete post-tests online.

### Interventions

The study compares five prospective parallel groups receiving three distinct interventions, delivered in various combinations (Table 1). Participants in Groups 1 and 3 will be offered (Interactive or Static) Web-based information and, following verification of completion, a sampler of HPDs will be supplied to them. Participants in Groups 2 and 4 will be offered (Interactive or static) Web-based information and asked to verify completion. Participants in Group 5 will simply receive a sampler of HPDs on completion of the pretest.

#### Interactive Web Intervention (IWI)

This intervention will include targeted messages focusing on farmer-friendly techniques for adopting use of HPDs, interactive learning techniques (e.g., sound level meter), role modeling techniques (e.g., farmer testimonials), and cognitive, demonstration, persuasion techniques. Intervention delivery is not linear; participants will select the sequence of features they visit, as well as the time spent in each feature and number of visits to the site. Their patterns of use will be tracked by the enrollment and data collection systems and used in analysis.

The standard (“static”) information promoting HPD use delivered via Internet will consist of a previously developed informational brochures (i.e., *Have You Heard?* [40] and *They’re Your Ears Protect Them* [41].

The proposed study will provide a sampler of HPDs to a sub-sample of each group of farmers receiving the Interactive and Static Web Interventions and to a group of farmers who do not receive a web based intervention. The sampler will include the most commonly-used types of devices (i.e., muffs, foam plugs, pre-molded plugs, and semi-aurals).

The study will include development of the informational Web site, inclusive of elements previously developed (e.g., video testimonials and HPD insertion techniques, animated graphics). Near final systems will be tested with a sample of the target population (confirmative testing interviews). Fidelity of the intervention is assured because delivery of information via the Internet ensures a consistent presentation of the Interactive and Static interventions.

### Outcome measures

Outcome measures will include self-reported frequency of HPD use and related attitudes/beliefs, measured at 6 and 12 months post-intervention. The outcome variables for the study are based on the Predictors of Farmers’ Use of Hearing Protection Model and include cognitive and affective factors that are specific to the behavior of HPD use (i.e., frequency of HPD use, perceived barriers, self-efficacy, access, interpersonal influences).

The HPD Use instruments (Appendix G) measuring the concepts from the theoretical model, together with their corresponding alpha reliability coefficients are described in Table 2. Development of these scales included pretest, revision, and review for construct validity by an expert panel; the process is described elsewhere [24,36]. All have alpha coefficients near or above .70. Additional variables measured will include demographic characteristics, functional hearing ability, satisfaction with the intervention, and social desirability bias (short form of the Marlowe-Crowne social desirability scale) [42].

**Table 2 Tab2:** **Scale Means, Standard Deviations, and Alpha Coefficients**

**Scale name**	**Number of items**	**Range of scores**	**Mean**	**Cronbach’s alpha**
Barriers^a^	13	1-6	2.61	.81
Benefits^b^	5	1-10	8.88	.82
Self Efficacy^a^	11	1-6	4.43	.75
Situational Influences^a^	11	1-6	4.07	.81
Norms^c^	4	1-3	2.33	.68
Modeling^d^	4	1-5	2.27	.81
Support^e^	4	1-3	1.41	.69
HPD Use^f^	4	0-100	27.50^g^	.89
Social desirability^h^	8	8-24	.^i^	.74

^a^Rating scale (1=strongly disagree; 6=strongly agree); ^b^Rating scale (1=slightly important; 10= highly important); ^c^Rating scale (1=not at all; 3=a lot); ^d^Rating scale (1=never; 3=usually); ^e^Rating scale (1=never; 3=often); ^f^HPD = hearing protection device; percent of time of use; ^g^43.2% report zero use; 56.8 percent report some use; ^h^Rating scale (1=yes; 2=no); ^I^not determined for this population.

### Analysis and sample size estimates

Power analysis was conducted using PASS software [43] to determine the sample size needed to provide 80% power to detect important effects that we expect to see in the research, based on comparisons between conditions with alpha of .05 two tailed, given findings from past studies. Given how low use of HPDs is among farmers, we expect to produce and detect changes of 13% in percent time use between conditions with a standard deviation of .3, thus an effect size d of .43 which is a bit smaller than what Cohen (1992) defined as medium sized. A sample size of 85 per group is needed to have 80% power to detect an effect size d = .43. With a second posttest at 12 months we have allowed for a loss of up to 40%, so will recruit 709 subjects total to retain 425 or 85 per group.

### Data analysis plan

Descriptive statistics will determine frequency distributions, percentage distributions, and means and standard deviations. Distributions of variables will be examined to detect and correct values outside of the legal range. They will also be examined for the normality of their distribution and transformed as appropriate so they meet the assumptions of the statistical analysis. Cronbach’s alphas will be used to assess internal consistency of multiple item scales as a measure of reliability. Scales with alphas of at least .63 will be considered usable. The various experimental groups will be compared on baseline values of variables. Independent variables found to differ between groups at baseline will be added to the analyses as covariates.

A random intercept mixed model will be used to explore the fixed effects of the three NIHL prevention interventions over time adjusting for age and gender as covariates. The model will include a random intercept for subjects to control for non-independence of repeated measures. A compound symmetric covariance structure will be specified in the model. Each of the outcomes: use of HPDS, attitudes, and beliefs will be modeled separately in order to investigate the effects of web interventions and mailed hearing protection devices. The data will be analyzed within two research designs. First will be the complete factorial design 2 (interactive vs. static web) x 2 (sent HPDs) x 3 (times: baseline, 6 months, and 12 months). This will not include the condition in which participants are simply sent HPDs. The second design will include all conditions in an incomplete factorial 3 (interactive web vs, static web vs. no web) X (sent HPDs) x 3 (times: baseline, 6 months, 12 months). SAS 9.3 (SAS Institute Inc., Cary, NC, USA) and SPSS 22 will be used for all analyses. A p-value of < .05 will indicate statistical significance.

#### Tests of hypotheses 1 and 2

Participants receiving interactive Web interventions will have higher HPD use and more favorable use-related attitudes/beliefs than participants not receiving Interactive Web interventions;Participants receiving the mailed HPD Intervention will have higher HPD use and more positive use-related attitudes/beliefs than participants not receiving the mailed HPD Intervention.

The dependent measures used for all the aims are quantitative variables: the individual’s percentage of time using HPDs, and relevant attitudes/beliefs, as outlined in Table 1. Either before or after transformation they will be normally distributed so will be analyzed by linear random intercept mixed models.

All analyses to test Hypotheses 1 and 2 will include baseline data collection and will focus on the tests of interactions of time with web format and with sending HPDs. Tests of these interactions with time will indicate whether changes over time are equivalent in different groups, for example whether participants exposed to the interactive web intervention increased use of HPDs more than participants exposed to the static web intervention. Follow-up analyses will present mean use and mean scores on attitudes/beliefs by time and condition as estimated by the mixed model. The same analysis focusing on different interactions with time will be conducted to test hypothesis 2. Naturally, they will test the interactions of time with provision of HPDs to test the hypothesis that provision of HPDs will increase use and improve use-related attitudes/beliefs.

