#### Test of hypothesis 4. There will be no interaction between intervention delivery mode (interactive vs. Static) and the mailed HPD intervention

Analyses to test Hypothesis 4 will be conducted by a 2 (Interactive Web vs Static Web) x 2 (providing HPDs) x 3 (times: within subjects) random intercept linear mixed model. The condition of mailed HPD intervention will not be included in these analyses. As with analysis of the other hypotheses, the focus is on the interaction(s) with time. Inclusion of a pretest time in the design and analysis means that the analysis is really about changes over time. In analyses to test Hypothesis 3, the key question is whether the changes over time are different in the group that receives both the Interactive Web Intervention and HPDs than would be expected by adding the effects of Interactive Web Intervention and supply of HPDs. The significance test of the three-way interaction will test this. We hypothesize that this three-way interaction will not be significant. However a significant interaction would be interesting, too.

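### Covariates are to be chosen by chance baseline differences, and leaving baseline unconstrained costs precision in the time-by-condition tests

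*Protocol article*

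**What the plan says.** Participants are allocated to five conditions by "random assignment of treatments in blocks produced by Stata software" (Random assignment to study conditions).

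The Data analysis plan names two covariates in advance, "adjusting for age and gender as covariates". It then adds a rule for further ones: "The various experimental groups will be compared on baseline values of variables", and "Independent variables found to differ between groups at baseline will be added to the analyses as covariates".

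The pretest enters the model as a response. The four-condition factorial is crossed "x 3 (times: baseline, 6 months, and 12 months"), and the five-condition design uses the same three visits. The model has a random intercept and a compound symmetric covariance.

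The tests of Hypotheses 1 and 2 "will focus on the tests of interactions of time with web format and with sending HPDs". The section on Hypothesis 4 describes the consequence plainly: "Inclusion of a pretest time in the design and analysis means that the analysis is really about changes over time". Nowhere does the article set baseline means equal across the randomised conditions.

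**The concern.** Two features of the plan bear on how baseline information is used.

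**Covariate rule.** With correct randomisation, any difference between conditions at baseline is a chance difference. Finding one says nothing about whether the variable predicts hearing protector use. The rule can therefore bring in variables that do not matter and pass over prognostic ones that happen to balance. It also means that the model is not settled until baseline data have been inspected.

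**Baseline as a free level of time.** When each condition has its own baseline mean, the time-by-condition test is a comparison of change scores. Randomisation guarantees that the baseline means are equal in expectation, and the model does not use that fact. What is at stake is precision that the pretest has already paid for, not validity.

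**Working it through.** **The plan's own figure.** Inputs from Analysis and sample size estimates: d = .43, two-sided alpha .05, power 80%, 40% loss.

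- n per group = 2(1.960 + 0.842)² / 0.43² = 2 × 7.849 / 0.1849 = 84.9, so 85.
- 5 × 85 = 425, and 425 / 0.6 = 708.3, so 709.

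Both stated figures reproduce and are not in dispute.

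**Effect of the covariate rule on the key test.** The time-by-condition estimate is a difference between conditions in mean within-person change. A covariate measured once and entered as a main effect is constant across visits, so it cancels. A simulation with 140 per group, correlation 0.6 and covariate slope 0.5 (all assumed) confirmed this:

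- Complete data: the shift in the 12-month estimate was about 10⁻¹⁶, which is zero to rounding.
- 20% random loss at each follow-up visit (1 − 0.8 × 0.8 = 36% by month 12): the shift had SD 0.014 against a standard error of 0.127, and 0.014 / 0.127 = 11% of one standard error.

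**How often the rule would act.** If k candidates are each tested at .05 and the tests are independent, the chance that at least one is flagged is 1 − 0.95^k: 23% for k = 5, 34% for k = 8, 37% for k = 9. The count, the threshold and the independence are all assumptions. Table 2 lists nine scales, but most of them are outcomes.

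**Cost of the unconstrained baseline.** Let σ² be the variance at one visit and ρ the correlation between visits, equal for all pairs under compound symmetry. Take complete data and work in units of 2σ²/n for a difference between two groups.

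One follow-up visit:
- change from baseline: 2(1 − ρ)
- common baseline mean: 1 − ρ²
- ratio: (1 + ρ)/2

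Average of 6 and 12 months:
- change from baseline: (1 + ρ)/2 + 1 − 2ρ = 1.5(1 − ρ)
- common baseline mean: (1 + ρ)/2 − ρ² = (1 − ρ)(1 + 2ρ)/2
- ratio: (1 + 2ρ)/3

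The article gives no ρ, so a range is shown. Power is for one follow-up visit, d = .43, 85 per group, normal approximation, taking the SD of .3 as the SD of level.

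| ρ | Variance saved, 12-month effect | Variance saved, average follow-up | Power, change contrast | Power, common baseline | n per group for 80%: change / common |
|---|---|---|---|---|---|
| 0.3 | 35% | 47% | 65.9% | 83.6% | 119 / 78 |
| 0.5 | 25% | 33% | 80.0% | 89.9% | 85 / 64 |
| 0.7 | 15% | 20% | 95.1% | 97.5% | 51 / 44 |

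Since 2(1 − ρ) exceeds 1 when ρ is below 0.5, the change contrast is then less precise than comparing follow-up values and ignoring the pretest.

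**Which tests this covers.** The power column uses the article's own planning basis, a comparison of two conditions. A main effect in the 2 × 2 design pools two conditions on each side, 170 against 170. If the effect is the same at both levels of the other factor, then at ρ = 0.3 the standardised effect is 0.43 × √(170/2) / √1.4 = 3.35, and power is about 92%. The proportional saving in variance depends only on ρ, so it is the same for main effects and for the interaction.

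**The case against.** The strongest reply is that the planned analysis is sound. A three-level time factor with time-by-condition interactions gives an unbiased, valid test in a randomised pretest-posttest trial, so the constraint is an improvement rather than the repair of an error. That stands. It is also true that:

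- The size of the gain rests on a correlation that the article does not give.
- The sample size section does not say whether the SD of .3 is of level or of change. If it is of change, the stated 80% already describes the planned contrast and there is no shortfall. The constraint would still gain precision.
- If the SD is of level, pairwise power reaches 80% once ρ is 0.5 or more.
- Age and gender are fixed in advance, so the criticism of covariate choice reaches only the added variables.

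A reader might go further and infer that the estimates and p-values for the main hypotheses hang on which covariates chance throws up. The article does not support this. It mentions no covariate-by-time terms, and a main effect barely touches a within-person contrast. Nor does the text say that the covariate set would change from outcome to outcome: the rule refers to independent variables and to the analyses as a whole. Selection uses baseline data only, so it is not model choice driven by treatment results.

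What the reply does not remove is that the rule serves no purpose under randomisation, and that the precision is available at no cost.

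**Conclusion.** The point holds as one of poor practice and lost efficiency. The baseline-difference rule does not identify prognostic variables and leaves the model unfixed, but its effect on the planned tests is nil with complete data and slight with dropout if covariates enter as main effects.

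The larger matter is the unconstrained baseline. For ρ from 0.3 to 0.7, a common baseline mean reduces the variance of the 12-month effect by 35% to 15% and of the average follow-up effect by 47% to 20%. A pairwise, single-visit change contrast falls below the stated 80% power only if the SD of .3 is the SD of level and ρ is under 0.5. These results assume compound symmetry, which the article states, together with complete data and the assumed range of ρ.

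It would be tempting to add that the interaction test suffers most. It does not lose more in proportion than the main effects, and Hypothesis 4 expects no interaction.

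**What to change.** 1. Delete the rule that adds covariates found to differ at baseline, and report baseline values by condition descriptively.
2. Keep age and gender as the pre-specified covariates.
3. Fit the three-visit model with one common baseline mean across the randomised conditions, so that condition effects appear only at 6 and 12 months. Alternatively, use the baseline score as a covariate and the 6- and 12-month scores as outcomes.
4. State the hypotheses as condition effects at follow-up under that model, including the web-format by hearing-protector interaction.

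The cost is wording in the analysis plan. No new data or participants are needed, and under the stated covariance structure precision improves at every ρ below 1.

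### Age and gender, entered as time-constant covariates, leave the condition-by-time tests of Hypotheses 1, 2 and 4 essentially unadjusted

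*Protocol article*

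**What the plan says.** The data analysis plan of the protocol article specifies a linear mixed model with a random intercept per participant and compound symmetry, to examine the "fixed effects of the three NIHL prevention interventions over time adjusting for age and gender as covariates". Its two factorial layouts cross web format and mailed HPDs with three times (baseline, 6 and 12 months). Age and gender stand outside both layouts. The same section adds, as further covariates, independent variables that turn out to differ between groups at baseline. It does not state how any covariate enters.

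The tests lie elsewhere in the model. Under the heading for Hypotheses 1 and 2, the analyses "will focus on the tests of interactions of time with web format and with sending HPDs". Under Hypothesis 4, "the focus is on the interaction(s) with time", and the deciding test is the three-way interaction of web format, HPDs and time. That section also says that the analysis is in effect about change.

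**The concern.** The adjustment and the test act on different parts of the model. A covariate that is constant over time and enters as a main effect explains differences in level between participants. The hypotheses concern differences in change within participants, from which such a term drops out. The rule for adding variables that differ at baseline has the same defect: its apparent purpose is to deal with imbalance, yet main-effect entry does almost nothing for the tested contrasts.

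At stake is what the results may claim. A reader told that the tests were adjusted for age and gender would suppose that a chance imbalance had been allowed for and that precision had been gained. For Hypotheses 1, 2 and 4 neither would be so to any useful degree.

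**Working it through.** **1. The plan's own figure.** The sample size section gives alpha .05 two-tailed, 80% power and "changes of 13% in percent time use between conditions with a standard deviation of .3, thus an effect size d of .43".

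- n per group = 2(1.96 + 0.842)² / 0.43² = 2 × 7.85 / 0.1849 = 84.9, so 85, as stated.
- 5 × 85 = 425, and 425 / 0.6 = 708.3, so 709, as stated.

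These figures reproduce and do not depend on how covariates enter.

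**2. Why the term cancels.** For participant i in group g at time t, write

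y(i,t) = μ(g,t) + β·x(i) + b(i) + e(i,t),

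with x(i) age or gender and b(i) the random intercept. Then

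y(i,t) − y(i,0) = μ(g,t) − μ(g,0) + e(i,t) − e(i,0).

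Both β·x(i) and b(i) are gone. With complete data and compound symmetry, the group-by-time estimate is the difference in mean change, so including x alters neither it nor its standard error.

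**3. Simulation.** From the documents: the 2 × 2 × 3 layout, random intercept, compound symmetry, d = 0.43, loss of up to 40%, and 709 / 5 ≈ 142 per group (4 × 142 = 568). Assumed, not in the documents: intraclass correlation (ICC) ρ = 0.5, and age and gender effects on level of 0.3 SD each. The quantity is the web-by-12-month coefficient in SD units (reference coding, so 142 v 142), over 60 simulated trials per row. Each cell gives mean estimate (mean SE).

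| Scenario | No covariates | Main effects | Covariate-by-time | Largest single-trial shift, main effects v none |
|---|---|---|---|---|
| Complete data | 0.4328 (0.1187) | 0.4328 (0.1187) | 0.4340 (0.1189) | about 1e-15 |
| 39% loss, unrelated to age | 0.4111 (0.1426) | 0.4114 (0.1426) | 0.4114 (0.1429) | 0.024 |
| 41% loss, depending on age | 0.4265 (0.1440) | 0.4268 (0.1440) | 0.4262 (0.1444) | 0.043 |
| Complete, constructed imbalance | 0.4911 (0.1187) | 0.4911 (0.1187) | 0.4349 (0.1195) | about 1e-15 |
| 44% loss depending on age, constructed imbalance | 0.4712 (0.1472) | 0.4780 (0.1472) | 0.4234 (0.1484) | 0.069 |

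Hand check of the first SE: √[2(1 − ρ) × 2/142] = √(2/142) = 0.1187. REML fits to three data sets with age-dependent loss changed the SE by under 1% when main effects were added (for example 0.14762 to 0.14701).

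**4. Size of an imbalance left in place.** The constructed rows shift age by 0.3 SD in the web arms and let age affect change by 0.2 per SD. The expected shift is 0.3 × 0.2 = 0.06, and 0.43 + 0.06 = 0.49, as the complete-data row shows. On the planning SD of .3 that is 0.06 × 30 = 1.8 percentage points, against a planned difference of 13. Under randomisation the age difference between two groups of 142 has SD √(2/142) = 0.119, so 0.3 lies about 2.5 SDs out. A one-SD imbalance would shift the estimate by 0.119 × 0.2 = 0.024 SD, or 0.7 points. The 0.2 is an assumption; the documents do not say that age or gender predicts change.

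**5. Conditioning on baseline instead.** At one follow-up with complete data, the variance is 2σ²(1 − ρ) for change and σ²(1 − ρ²) given baseline. The ratio of standard errors is √[(1 + ρ)/2]:

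- ρ = 0.3: 0.81
- ρ = 0.5: 0.87
- ρ = 0.7: 0.92

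A separate simulation at ρ = 0.5 gave a more modest gain: the empirical SD of the 12-month effect fell from 0.125 to 0.115, a ratio of 0.92.

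**The case against.** The strongest reply is that the article never says main effects only. It is a condensed text, and a full protocol or SAP not shown here may hold covariate-by-time terms. That stands as a limit: the point rests on the plain reading. It is still the natural reading, because the section spells out which factors cross with time and age and gender are not among them.

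A reader might infer that the tests are biased. The documents do not support that. Allocation is random, the contrasts are unbiased on average without any covariate, and their standard errors already cover chance imbalance. The bias in the table required a systematic imbalance built into the simulation.

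A reader might also infer that every hypothesis is affected. The section on Hypothesis 3 describes an effect of number of views and names no interaction with time; only a general remark under Hypothesis 4 points that way.

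Nor is much precision lost merely by omitting covariate-by-time terms. With no true link between the covariates and change, adding them raised the SE from 0.1187 to 0.1189. The Background reports no significant relation of age to HPD use in two studies and conflicting results for gender, and those concern level of use, not change.

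Finally, main effects are not idle: they adjust the mean levels by time and condition that the plan will also present, and with dropout they enter the interactions slightly. All of this lowers the weight of the point. None of it makes the stated adjustment act on the tests.

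**Conclusion.** The point holds in limited form. If age, gender and any variable that differs at baseline enter as main effects, the condition-by-time tests of Hypotheses 1, 2 and 4 are unadjusted exactly with complete data. They are nearly so at the planned loss: single-trial shifts were at most 0.07 SD, and the SE was practically unchanged at an assumed ICC of 0.5. Calling those tests adjusted would mislead. Validity is not in question. The loss is the intended control of chance imbalance, likely under one percentage point for a one-SD age imbalance on the assumptions above, and some precision. Conditioning on baseline would recover about 8 to 19% of the standard error, on the formula for an ICC between 0.7 and 0.3. That gain comes mainly from the baseline value, not from age and gender. This is a modest correction, worth making before analysis because it is cheap.

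**What to change.** For Hypotheses 1, 2 and 4, do one of the following and state it in the model description.

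- **Preferred:** model the 6- and 12-month values given the baseline value, with age and gender as covariates. The tested term becomes the condition effect at follow-up (for Hypothesis 4, web format by HPDs), and the covariates then act on it. This is a different estimator from change from baseline and usually a more precise one, so the hypothesis sections need rewording. A participant with no follow-up value contributes nothing to it.
- **If baseline stays an outcome time point:** add age-by-time and gender-by-time terms, and the same for any other fixed covariate retained. For age and gender this costs 2 covariates × 2 follow-up contrasts = 4 degrees of freedom. It gains precision only if age or gender predicts change.

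The two are not interchangeable, so choose one before the data are analysed. If the full plan already contains such terms, one sentence saying so settles the matter. Either choice uses only data already to be collected and leaves the sample size as it is.
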